#### Fish oil supplementation

For maximum adherence and minimal cost, administration of EPA and DHA will occur via unencapsulated fish oil taken on fruit juice or vegetable juice. Participants will be required to float 20 ml fish oil (Melrose Omega 18/12 - Aust L93186; Melrose Health, Victoria, Australia) on 30-40 ml juice, or any other flavoured, non-fizzy drink. The fish oil concentrate is flavoured with lemon and lime to mask the fish scent and taste. To avoid any potential side effects associated with the consumption of fish oil, participants are asked to consume the fish oil on juice with breakfast to avoid consumption on an empty stomach. If this dosage is not tolerated, the frequency and volume may be adjusted in conjunction with the research Dietitian, or alternatively fish oil capsules will be offered as an alternative to provide similar concentrations of EPA and DHA as the liquid oil (a total of 17 capsules per day, Melrose - Omega, Aust L156237; Melrose Health, Victoria, Australia).

The anti-inflammatory dose of fish oil selected for the intervention group provides ~3.6 g EPA and ~2.4 g DHA per 20 ml. The low-dose fish oil selected for the control group will be prepared to contain 10% of the active dose, which is also flavoured with lemon and lime to assist in maintaining participant blinding (~0.36 g EPA and ~0.24 g DHA per 20 ml). As with the intervention group, those participants in the control group who refuse to continue with the allocated dose of liquid oil will be offered fish oil capsules providing the equivalent dosage of EPA and DHA.

As an inpatient, at baseline, the participant's fish oil will be dispensed by each hospital's pharmacy and administered on the inpatient medication round. The pharmacy will also dispense outpatient supplies alongside other discharge medications.

#### Fortnightly visits

The research Dietitian will perform fortnightly home visits to all participants (intervention and control) over 12 weeks to perform dietetic care and maximise participant nutritional status by way of reviewing the nutrition care plan, dietary counselling and education, monitoring participant weight, ensuring energy and nutrient requirements are achieved as well as monitoring potential gastrointestinal side effects from the dose of fish oil.

### Sample Size Considerations

Quality of life is the primary outcome in this study and was selected because quality of life is an important determinant of future outcomes. It is recommended that half the baseline standard deviation of raw scores provides an appropriate estimate of the minimally clinically important difference for quality of life, and this form of estimation is useful in the absence of direct measurements of important change [48]. Using this method, the minimally clinically important difference was calculated to be approximately 2 points for the AQoL. A sample size of 64 participants per group is expected to achieve this difference between the two groups (power 80%, alpha = 0.05). To allow for deaths and withdrawals (5% and 10% respectively), 150 participants will be recruited (75 per group). This sample size will provide 92% power to detect a difference of 3 (effect size of 0.6) on the appetite questionnaire.

### Statistical Analysis

All statistical analyses will be performed using SPSS for Windows, version 18 (SPSS Inc, Chicago, USA). Data will be entered into a centralised secure database with remote web access (CareSearch Research Data Management System - http://www.caresearch.com.au) and will subsequently be exported into SPSS software for analyses. Primary analysis for this study will be undertaken using intention to treat principles. Independent samples t-tests, Mann-Whitney U test and Chi-square test of association will be used as appropriate to compare groups at baseline. To determine differences between the groups at the primary end-point (12 weeks), ANCOVA or logistic regression will be used with models adjusted according to potential confounders.

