#### Other assessments

##### Quality of life (baseline, 6 and 12 weeks; 12 month follow-up)

Health-related quality of life will be assessed using the Assessment of Quality of Life Instrument (AQoL) [44], a 15 item survey with high internal consistency covering five domains: illness, independent living, social relationships, physical senses and psychological well-being. The resultant summary score can be transformed into a utility index, and subsequently, quality-adjusted life years calculated.

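### The 12-week ANCOVA named as primary makes no use of the 6-week AQoL and, unless missing scores are imputed, leaves out participants without a 12-week score despite the intention-to-treat label

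*Protocol article*

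**What the plan says.** All references are to the protocol article.

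- **Statistical Analysis** sets the principle: "Primary analysis for this study will be undertaken using intention to treat principles". It then names the method and the visit: "To determine differences between the groups at the primary end-point (12 weeks), ANCOVA or logistic regression will be used", with adjustment for potential confounders. The section gives no rule for participants who lack the 12-week value.
- **Sample Size Considerations** names the primary outcome: "Quality of life is the primary outcome in this study". It requires 64 per group and then adds an allowance for loss: "To allow for deaths and withdrawals (5% and 10% respectively), 150 participants will be recruited (75 per group").
- The AQoL schedule is in the heading of its own subsection under **Other assessments**: "Quality of life (baseline, 6 and 12 weeks; 12 month follow-up"). A 6-week score is therefore planned for every participant, but no section gives it a part in the primary comparison.
- **Randomisation and Blinding** stratifies allocation by hospital site and by oily fish intake.

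**The concern.** An ANCOVA at one visit needs an outcome value at that visit. Without imputation, a randomised participant with no 12-week AQoL adds nothing to the estimate. The analysis then compares those who stayed, which is not what the intention-to-treat label beside it promises.

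Loss in this population is unlikely to be unrelated to health. The Background gives 30% mortality at 12 months after surgery, and the sample size allows for deaths. The article also monitors gastrointestinal effects of the oil and provides for participants who will not continue with the liquid. The active arm receives ten times the EPA and DHA of control, so reasons for leaving could differ between arms even if the numbers do not.

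At stake is the accuracy of the primary estimate. The 6-week AQoL is the most recent measure of how a later dropout was faring, and the named method ignores it.

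**Working it through.** **1. Reproduce the plan's sample size.** Inputs from Sample Size Considerations: a minimally important difference of about 2 AQoL points, set at half the baseline SD, so the implied SD is 4 and the standardised effect is 2/4 = 0.5; alpha 0.05; power 80%. A two-sided two-sample t-test needs 63.8, so 64 per group. This matches. Inflation: 64/(0.95 × 0.90) = 74.9, so 75 per group and 150 in total. This also matches.

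**2. Which number carries the stated power?** For the appetite questionnaire at effect size 0.6, a t-test gives 92.0% power with 64 per group and 95.5% with 75. The article states 92%, so its power counts only those expected to remain.

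**3. How many could be omitted?** 150 × 0.15 = 22.5, or 150 × (1 − 0.95 × 0.90) = 21.75: about 22. This is an upper figure, reached only if all planned loss falls by week 12. By the plan's own split, 5 of the 15 percentage points are deaths.

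**4. Does using week 6 add power?** Assume a common correlation r between visits. Given baseline, the partial correlation of the 6- and 12-week scores is ρ = (r − r²)/(1 − r²). Let n_c be the completers per arm and n_l those lost after week 6. The effective n per arm is then 1/[(1 − ρ²)/n_c + ρ²/(n_c + n_l)].

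Example with r = 0.5, n_c = 75 × 0.85 = 63.75 and n_l = 11.25: ρ = 0.333, and effective n = 1/[(0.889/63.75) + (0.111/75)] = 64.8.

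| r | Effective n, all loss after week 6 | Power, completers | Power, with week 6 |
|---|---|---|---|
| 0.3 | 64.3 | 84.1% | 84.4% |
| 0.5 | 64.8 | 90.3% | 90.8% |
| 0.7 | 65.4 | 97.7% | 98.0% |

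The gain is at most about 0.5 percentage points, and smaller if some loss precedes week 6.

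**5. Does using week 6 reduce bias?** Simulations used a true 12-week effect of 0.50 SD and about 14-15% lost in each arm. Assumed, because the article gives none of these: visit correlations 0.45-0.70, and loss depending on the 6-week score with a log-odds slope of 1 to 2 per SD.

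| Who is lost | Completer ANCOVA | Likelihood model using week 6 |
|---|---|---|
| Both arms depend on 6-week score | 0.48-0.49 | about 0.50 |
| Only control depends on it; active loss random | 0.41-0.45 | about 0.50 |

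Attenuation: (0.50 − 0.49)/0.50 = 2% to (0.50 − 0.48)/0.50 = 4% when the mechanism is shared, and (0.50 − 0.45)/0.50 = 10% to (0.50 − 0.41)/0.50 = 18% when it acts in control only. With SD 4, these are 0.04-0.08 and 0.20-0.36 AQoL points. In one pair of runs the estimates' SD was 0.158 for completers and 0.155 with week 6, so there is no precision penalty.

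The table has all loss after week 6. Weaker settings gave up to 0.47 in the control-only case. With half the loss before week 6 and random, one control-only run gave 0.474 for completers. With half the loss before week 6, the likelihood model gave 0.46-0.50. If only active-arm loss depended on 6-week status, the bias would run the other way and inflate the effect.

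**6. Under no true effect.** With dropout driven by the 6-week score (correlations 0.5-0.7), completer ANCOVA was biased by about 0 when loss rates were equal, and by about 0.08-0.18 AQoL points when they differed by 10 percentage points. That is 4-9% of the 2-point difference.

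**The case against.** The strongest reply is that the article never says complete-case. It says intention to treat, and ANCOVA is compatible with multiple imputation, including imputation that uses the 6-week score. Rules for missing data may sit in a full protocol or analysis plan that is not shown, and their absence from an article is no fault. This stands. A reader might infer from steps 1 and 2 that the intended analysis is complete-case, but inflating for loss is routine however missing scores are later treated. The documents do not support that stronger reading. What they do fix is a primary model at a single visit, and that choice can be judged on its own.

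A second reply is that the larger bias comes from a chosen scenario. Both arms take 20 ml/day of flavoured oil, double-blind, with the same care and visits, and the article calls gastrointestinal effects unlikely at the dose. This also stands: nothing in the article shows that only control loss depends on 6-week health, so a flat 10% bias should not be claimed. The shared-mechanism figure of 2-4% belongs beside it.

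Third, a repeated-measures model is not a complete remedy. It recovers information only from those lost after week 6, and it implicitly gives people who have died a 12-week quality of life. Both limits are accepted. The article also does not say whether the 15% refers to 12 weeks or 12 months, or whether withdrawal means leaving the study or only stopping the oil, so 22 is a ceiling.

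**Conclusion.** The point holds in limited form. The named single-visit ANCOVA does not by itself deliver the intention-to-treat comparison for those lost before 12 weeks, and it leaves scheduled data unused. The likely harm is modest attenuation, about 2-4% with a shared loss mechanism and about 10-18% with a control-only one, and less when part of the loss precedes week 6. The direction would reverse if only the active arm were affected. The likelihood model was closer to the true effect in every setting compared.

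These sizes rest on assumed correlations, assumed dropout slopes and loss that depends on observed 6-week status. If loss depends on unobserved 12-week health, neither method is protected. The sample size is unaffected: 150 already covers the planned loss, and the change is not a power argument. It is a worthwhile and cheap improvement, not a fatal defect.

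**What to change.** Make the primary analysis a likelihood-based repeated-measures model of AQoL at 6 and 12 weeks. Include baseline AQoL, treatment, visit, treatment-by-visit and the randomisation strata (site and fish intake). Report the 12-week treatment contrast as the primary result and keep the single-visit ANCOVA as a sensitivity analysis.

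Two additions are needed because the model does not cover them:

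- State separately how participants who die before 12 weeks enter the primary comparison.
- Add a sensitivity analysis for participants lost before week 6, who have no post-baseline AQoL.

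The change should be made before unblinding. It needs no extra participants, visits or data, and SPSS, the package already named, has a mixed-model procedure. The costs are slightly more analysis work and reliance on a missing-at-random assumption, which should be stated openly.

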### Time Frame

This study has a 3.5-year time frame. It is expected that recruitment will commence late 2010 and continue until mid 2012. An additional 12 months will then be required to finalise data collection and six months to complete data analysis and prepare manuscripts for submission to peer reviewed scientific journals.

## Discussion

To the best of our knowledge, the ATLANTIC trial is the first of its kind to provide fish oil and individualised nutrition therapy as an intervention to address the deterioration in nutritional status which commonly occurs in PFF patients. This trial will explore more detailed information about the key markers of cachexia than previous work in this population group, particularly concerning the magnitude of inflammation experienced post PFF.

This trial will commence earlier than previous research where fish oil has been explored in the treatment of cancer cachexia. Given that the natural process of bone healing is influenced by a variety of systemic and local factors, including an early inflammatory phase [49], the intervention will commence day 7 following PFF surgery with an ongoing intervention phase of 12 weeks. The use of anti-inflammatory medication throughout the first week of bone healing may alter this natural inflammatory process and potentially inhibit normal bone healing [49]. Furthermore, the literature provides convincing evidence that markers of cachexia, including poor appetite [8,50], involuntary weight loss, in particular lean muscle [51,52], increased REE [53-55] and decreased albumin [55,56] are commonly observed in patients recovering from PFF.

Evidence exploring the inflammatory response post PFF surgery in this population group is scant. Previous research using fish oil as an intervention for cachexia has used the model of pancreatic cancer, however there have been considerable limitations in this research including heterogeneous samples representing mixed tumour types and severity, the use of variable and largely insufficient doses of EPA, and in some cases, the administration of fish oil for short durations [57]. Furthermore, the likelihood of demonstrating an effect with fish oil for patients recovering from PFF surgery is likely to be more favourable than patients with advanced cancer given the more acute nature of the injury. With evidence now suggesting a persistent inflammatory response in patients post PFF surgery, and that conventional nutrition support alone is unconvincing, in an attempt to dampen the inflammatory response, it is a logical extension to evaluate whether patients recovering from PFF surgery respond positively to fish oil as an intervention in concurrence with individualized nutrition support.

It is rare that PFF patients receive any significant level of nutrition support as part of standard care following their acute care admission. A major strength of the ATLANTIC trial is that it takes a comprehensive approach to nutrition management where all participants receive individual dietary counselling and nutrition education from an Accredited Practicing Dietitian. This includes the provision of dietary education and counselling in the way of dietary modifications, food fortification and oral supplementation to ensure individual energy, protein and other nutrient requirements are achieved. This is particularly critical given the lack of evidence that oral supplementation alone is effective at improving clinical outcomes in this patient group [16].

To minimize the devastating consequences of cachexia as well as secondary hospital admissions, it is critical that adequate rehabilitation and nutrition support services post PFF surgery are provided. The results of this trial will assist clinicians in the development of more effective and alternative treatment methods, such as an anti-inflammatory dose of fish oil post PFF surgery which may ultimately result in a reduction in systemic inflammation, weight loss, particularly muscle mass, improvements in nutritional status, mobility, independence and quality of life among these patients.
